### Study population

All patients 70 years or older admitted to the participating wards will be informed about the TRADE project. In every study center, the TRADE Study team consists of trained study nurses and research assistants, supported by study physicians. Once consent is obtained, participants will be assessed by trained assessors.

Admissions to acute care will be regularly screened for eligibility for the study. In addition, awareness of patients and caregivers will be raised by putting up advertising posters and adding an informative flyer about the TRADE Study to the regular hospital admission folder which also refers to more information on the website.

In addition to patients, their primary caregivers will also be included in the study. We defined primary caregivers as follows: everybody with a close personal relationship to the patient such as partners and other family members but also close friends, confidents, neighbors or long-term legal guardians as identified by the patients. During the observational part of the study primary caregivers were asked for participation whenever possible. As caregiver’s participation is a key element for a successful intervention, their participation is mandatory during the pilot intervention part of the study.

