### Sample size

The sample sizes for both the observational study and the pilot intervention trial were chosen based on feasibility considerations. Robust sample size estimations were not possible because of the pilot character of the study and missing preliminary information. Power analysis for the intervention study was additionally based on descriptive results from the observational part.

For the pilot study we will include 500 patients in all four study centers (125 patients each within 12 months), including an estimated dropout rate of 20%. With preliminary results of the observational study and the expected sample size of 400 (excl. drop-outs) we conducted power analyses for the primary outcomes delirium incidence and cognitive function. In the control group of the pilot intervention study we would expect an incidence of delirium of about 6% and of cognitive impairment of about 41%. Using a two-sided chi-square test at a significance level of 5% with a power of at least 80%, one should be able to show a reduction in delirium incidence in the intervention group to 0.9% and in cognitive impairment incidence to 27.7%.

Patients with an unfamiliar discharge environment and cognitive impaired patients will be preferably included, as they are the main focus of the project having a high risk of delirium.

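### Preferential inclusion of high-risk patients has no rule holding it equal before and after crossover, so case mix can differ between phases and bias the overall effect in either direction

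*Protocol article*

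**What the plan says.** The selection rule stands at the end of the Sample size section: "Patients with an unfamiliar discharge environment and cognitive impaired patients will be preferably included, as they are the main focus of the project". The reason given is their high risk of delirium. No target share, order of approach or reference to study phase follows.

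Other parts of the article bear on this:

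- **Study population and Inclusion criteria.** Everyone aged 70 or older on the participating wards is to be told about the project, and admissions are screened regularly by a study team of nurses and research assistants. In the pilot, eligible patients are those within three days of planned discharge. Caregivers were asked to join the observational cohort where possible; for the pilot, "their participation is mandatory during the pilot intervention part of the study".
- **Stepped wedge design.** All four centres begin without the intervention. The first crosses over after 12 weeks and the others at 8-week steps. The order is pre-defined, not randomised.
- **Main results of the development part.** Discharge personnel are trained around crossover, and posters are put up on the wards.
- **Sample size.** Planning rates for the pilot's control group are 6% for delirium and 41% for cognitive impairment, based on the observational cohort. The detectable rates are 0.9% and 27.7%, with 400 patients analysed.
- **Statistical analysis.** Mixed models that account for the stepped wedge design are planned, together with analyses by centre and subgroup analyses by discharge environment and cognitive status.

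**The concern.** In a stepped wedge with individual enrolment, the treatment contrast compares patients recruited before a centre's crossover with patients recruited after it, alongside concurrent comparisons between centres. This is fair only if the same kind of patient is enrolled in both phases.

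An open preference for two high-risk groups leaves that to local discretion. It could be relaxed to reach 125 patients per centre in 12 months, or sharpened once delirium training has begun. Calendar drift common to all centres can be absorbed by period effects, where the model contains them. A change at a centre's own crossover cannot, because it coincides with the intervention. Randomising the entry order would not remove it either.

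At stake is the overall estimate for both primary outcomes. Cognition is the more exposed, since one of the two selection traits is impaired cognition itself.

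**Working it through.** **1. The plan's own figures.** Inputs from the Sample size section: two-sided chi-square test, alpha 5%, 400 analysed. The split is not stated, so 200 per condition is assumed.

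Power = Φ{ [ |p1 − p2|·√n − 1.96·√(2·p̄·(1 − p̄)) ] / √(p1(1 − p1) + p2(1 − p2)) }

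- Delirium, 6% to 0.9%: p̄ = 0.0345. (0.721 − 0.506)/0.2556 = 0.843, so power is 80.0%.
- Cognitive impairment, 41% to 27.7%: p̄ = 0.3435. (1.881 − 1.316)/0.6650 = 0.849, so power is 80.2%.

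Both figures reproduce. With control periods of 12, 20, 28 and 36 weeks out of an assumed 52, the control share is 96/208 = 46%, and power is 80.7% and 80.1%. The even split is therefore not critical.

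**2. Delirium: case-mix shift with no intervention effect.** The section on patients with cognitive impairment expects about 40% of inpatients to be impaired, which is used here as the starting share. The overall rate is 6%. The risk ratio k for impaired against other patients is not given, so 2 to 4 is assumed.

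Risk in other patients = 0.06/(0.4k + 0.6). Change in the overall rate for a 20-point shift = 0.20·(k − 1)·(risk in other patients).

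| k | Risk, others | Risk, impaired | Rate at 40% impaired | Rate at 60% impaired | Change (points) | Share of 5.1-point target |
|---|---|---|---|---|---|---|
| 2 | 4.3% | 8.6% | 6.0% | 6.9% | 0.9 | 17% |
| 3 | 3.3% | 10.0% | 6.0% | 7.3% | 1.3 | 26% |
| 4 | 2.7% | 10.9% | 6.0% | 7.6% | 1.6 | 32% |

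If the impaired share rises after crossover, this hides benefit. If it falls, it imitates benefit.

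**3. Cognition: impairment analysed as a status at follow-up.** Suppose case mix alone makes the phases 41% and 50%. With p̄ = 0.455 and n = 200: (1.273 − 1.380)/0.7014 = −0.153, giving a significant result 44% of the time with no intervention effect. The calculation is the same whichever phase has the higher rate.

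This 9-point gap equals the shift in the share impaired at entry only if entry status carries over one-to-one to follow-up. If the follow-up probabilities in the two strata differ by 0.7 instead (assumed), the share would have to shift by 9/0.7 = 12.9 points. The calculation uses the article's unadjusted chi-square, not the planned mixed model, so it indicates scale and is not a forecast.

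**4. If the control rates are higher than planned.** The article gives no alternative rates, so these are assumed.

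| Delirium control rate | Detectable rate at 80% power | Power, same relative reduction (0.9/6 = 0.15) | Power, same 5.1-point drop |
|---|---|---|---|
| 6% | 0.9% | 80% | 80% |
| 8% | 1.9% | 90% | 61% |
| 10% | 3.1% | 96% | 49% |
| 15% | 6.4% | over 99% | 34% |

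For cognitive impairment, control rates of 50% and 60% give detectable rates of 36.2% and 46.1%. Enrichment alone therefore need not weaken the study; it depends on the scale on which the effect is held constant.

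**The case against.** The strongest reply has four parts.

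- **The mechanism is inferred.** Ward training is aimed at discharge personnel, while screening belongs to a separate study team, and all older patients on the wards are to be informed. This stands in part: the article does not say that recruiters know the phase or that training alters their choices. But entry order is fixed in advance, posters hang on the wards, and no masking is described. Informing everyone does not settle who is then preferred.
- **Covariates are ordinary analysis-plan content.** This also stands. The article's silence on covariates is not held against it, and its Covariates section and baseline MoCA show that relevant data are collected. The subgroup analyses on the same two traits do show effects within strata. They leave the overall estimate unadjusted, however, and no analysis plan can undo how patients were enrolled.
- **The sizes are assumed.** True, and for delirium they are well below the target difference even with a 20-point swing. The cognition figure also needs the outcome to be follow-up status; the article speaks of incidence, which could mean new impairment.
- **This is a pilot.** Sample size rests on feasibility and all tests are called hypothesis generating. That limits the consequence. It does not remove it, because the results are meant to found a confirmatory study.

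A reader might go further and infer that the 6% and 41% are the wrong control rates. The documents do not support that. They present the rates as expectations for the pilot's control group, call the cohort's criteria and assessments comparable, and nowhere say that the cohort lacked the preference. That 41% lies close to the 40% expected among inpatients suggests an unenriched rate but does not prove it. Mandatory caregivers and the shorter inclusion window are real differences, but the direction of their effect is unknown.

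**Conclusion.** The point holds as a weakness in a stated recruitment rule: the preference is discretionary, and nothing keeps it equal across phases in a design where every centre moves from control to intervention in a known order. The resulting bias can go either way.

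Under the assumptions shown, it amounts to about 0.9 to 1.6 points of delirium against a target of 5.1. For cognition it could be larger: a 44% chance of a significant result with no effect, if impairment is analysed as a status and case mix alone separates the phases by 9 points.

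Three tempting conclusions are not supported: that the preference will in fact be applied differently, that the bias favours the intervention, and that the power statement is invalid. The power figures reproduce. The planning rates may not apply if the pilot is enriched relative to the cohort, and the article leaves that open. The matter should be corrected, with weight suited to an exploratory pilot.

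**What to change.** 1. Replace the open preference with consecutive approach of all eligible patients. If enrichment is wanted, use fixed quotas for discharge environment and cognitive status that are identical in every centre and in every period before and after crossover.
2. Include discharge environment and baseline MoCA as fixed covariates in both primary mixed models. If the analysis plan already does so, a sentence in the article is enough.
3. Report the mix of the two strata by centre and period, so that any shift at crossover can be seen.
4. State whether the 6% and 41% describe the preferentially recruited, caregiver-accompanied pilot population. If they do not, show the detectable rates over a range of control rates.

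The cost is one recruitment instruction and a few lines in the analysis plan. MoCA is already measured at baseline, and the planned subgroup analysis already requires discharge environment to be recorded. Quotas may slow recruitment slightly.

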### Stepped wedge design

For the pilot intervention study a stepped wedge design is used [52]. All clusters start without intervention. While the first cluster starts after 12 weeks, every other cluster follows after another 8 weeks until all four clinical partners have started. Please see also Table 2.

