**Fig. 2 Fig2:**
[figure not shown]
Delirium prevention and intervention strategies with eight major items (8-item-program)

Analysis of focus groups and expert workshops confirmed the a priori hypothesis that the implementation of the intervention should not only focus on hospital staff, but also on patients and caregivers alike. Before starting the intervention, gatekeepers will be identified in all participating centers in order to record the local structures and discharge processes at the beginning and at the end of the intervention phase, to be able to draw a comparison. With beginning of the intervention, all identified healthcare personal involved in the discharge process will be trained. Because discharge structures differ from hospital to hospital, multipliers, called champions, will be identified and trained at a maximum of 3 weeks before start of the intervention in each participating center to advise the rest of the staff involved in discharge procedures such as physicians, ward nurses, social workers, ward secretaries and others. This *train the trainer* approach consists of several steps. In a first step awareness for the study, the relevance of delirium and the motivation to participate in the intervention has to be promoted. In a second step, champions will be constantly supported to adhere to the intervention by regular video or telephone meetings with the project team. The other health care professionals will be also informed about delirium and the interventions in a short training session.

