In addition to the focused training, discharge managers and associated clinical disciplines will be provided with educational material as well as with prepared communication strategies to facilitate focused briefing to caregivers and patients. The educational materials consist of the following:A handbook for discharge managers and health care professionals: It summarizes general information on delirium risk factors and clinical impact in acute care hospitals. In addition, it outlines the 8-item-program and supports professionals providing a conversation guide for structured information provision to patients and primary caregivers.A check list for the discharge procedure for health care professionals.An educational flyer for primary caregivers: It includes all essential information on non-pharmacologic intervention strategies in the 8-item-program. Primary caregivers will be encouraged to deliver the intervention and support patients around hospital discharge. Flyers will be also used to generate awareness in other professionals e.g. transport service staff.A “Dos and Dont’s” poster for health care professionals: They will be placed in highly frequented places in the participating departments and present important principles of delirium friendly discharge and links to further information materials supplied by the TRADE study.“1-min-information” posters for health care professionals (following the “One minute Wonder” by Schmidt & Krueger [21, 22]): These are different posters that are displayed at highly frequented places in the participating departments and where persons wait for a maximum of 1 min (e.g. coffee machine). They contain brief information on delirium in general and delirium friendly discharge strategies with focus on one topic on every poster. Posters will be exchanged weekly to ensure ongoing attention to the project and to refresh knowledge on the topics.Online information videos for health care professionals as well as for caregivers with expert interview concerning delirium in general and in the context of discharge and transfer.

A summary of key components of the intervention in the context of the participant’s hospital treatment timeline can be found in Fig. 3:

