**Table 2 Tab2:**
[figure not shown]
Stepped wedge design and intervention entry in the pilot intervention trial. Legend: Control phase in grey parts of the table, intervention phase in blue parts of the table

During the observational study, imbalances in the distribution of participants insured by the AOK health care insurance among the different study centers were recognized. The balanced allocation of AOK health care insurance holders is an important feature for health economic evaluation. To minimize these imbalances for the pilot intervention study, a pre-defined cluster entry as given in Table 2 was chosen rather than a randomized approach.

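### No roll-out window after each centre's switch: if uptake is gradual, a 0/1 treatment effect adjusted for calendar time could understate the established effect

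*Protocol article*

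**What the plan says.** Timing (Protocol article, Stepped wedge design): "While the first cluster starts after 12 weeks, every other cluster follows after another 8 weeks until all four clinical partners have started". The Sample size section plans "125 patients each within 12 months". The Table 2 legend gives two states: "Control phase in grey parts of the table, intervention phase in blue parts of the table". Neither that legend nor the surrounding text mentions a transition period; the table itself is not visible in the copy reviewed.

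Delivery (Main results of the development part): champions are trained no more than 3 weeks before their centre starts, so that they can advise colleagues. For everyone else, "With beginning of the intervention, all identified healthcare personal involved in the discharge process will be trained". Champions then receive continuing support. Single-topic posters rotate: "Posters will be exchanged weekly to ensure ongoing attention to the project and to refresh knowledge on the topics". The Discussion describes the train-the-trainer approach as indirect.

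Analysis (Statistical analysis): mixed models are to account for the stepped wedge, with a logit link for binary and an identity link for continuous outcomes. How exposure is coded is not stated. All tests are called hypothesis generating.

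**The concern.** Patients discharged just after a switch may meet a ward where only the champions are fully prepared. A two-phase design puts them in the intervention phase all the same.

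This matters more in a stepped wedge than in a parallel trial. Once calendar time is adjusted for, the comparison depends on weeks when some centres have switched and others have not. For each centre those are mostly the first weeks after its own switch, so roll-out falls where the design draws most of its information.

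The article's abstract presents the pilot as the foundation for a confirmatory study. A diluted effect estimate would be carried into the planning of that study.

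**Working it through.** **The plan's own figure.** The Sample size section takes control rates of 6% (delirium) and 41% (cognitive impairment), intervention rates of 0.9% and 27.7%, 400 analysed patients, a two-sided 5% chi-square test and power of at least 80%. With 200 per group, power = Φ[(difference − 1.96·SE₀)/SE₁], where SE₀ is pooled and SE₁ unpooled:
- Delirium: (0.051 − 1.96 × 0.01825)/0.01807 = 0.843, power 80.0%.
- Cognitive impairment: (0.133 − 1.96 × 0.04749)/0.04702 = 0.849, power 80.2%.

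The figure reproduces, with no slack.

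**Exposure.** Switches fall at weeks 12, 20, 28 and 36. Reading 12 months as 52 weeks, centre exposure is 40, 32, 24 and 16 weeks, or 112 of 208 centre-weeks (54%).

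**Where the weight falls.** Assumptions: even accrual, fixed centre and period effects, one 0/1 indicator. Each treated centre-week is weighted in proportion to r = 1 − centre mean − period mean + overall mean. The centre means are 40/52, 32/52, 24/52 and 16/52. The period means are 0, 0.25, 0.5, 0.75 and 1 over periods of 12, 8, 8, 8 and 16 weeks. The overall mean is 0.5385.
- r in the first 8 weeks after each switch: 0.519, 0.423, 0.327, 0.231 (sum 1.5).
- Sum of r over all treated weeks: 8 × (0.519 + 0.692 + 0.519) + 16 × 0 = 13.85.
- Share of the first 8 weeks: 8 × 1.5/13.85 = 87%, from 32/112 = 29% of treated centre-weeks.
- Share of the first 4 weeks: 4 × 1.5/13.85 = 43%, from 16/112 = 14%.
- Calendar weeks after 36 (64/112 = 57% of treated weeks): net weight zero.

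**Loss under a linear ramp from zero.** For ramps up to 8 weeks the average shortfall within the ramp is one half, so loss = 0.5 × weight in the ramp:
- 2 weeks: 0.5 × 0.217 = 11%.
- 4 weeks: 0.5 × 0.433 = 22%.
- 8 weeks: 0.5 × 0.867 = 43%.

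**Random centre effect.** The expected estimate is the generalised-least-squares value (X′V⁻¹X)⁻¹X′V⁻¹y, with 100/52 analysed patients per centre-week and an assumed ICC of 0.001 to 0.2. The share of the full effect recovered is:

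| Effect after switch | With period effects |
|---|---|
| Immediate | 1.00 |
| 2-week ramp from zero | 0.89-0.92 |
| 4-week ramp from zero | 0.79-0.85 |
| 8-week ramp from zero | 0.57-0.69 |
| 4-week ramp from half effect | 0.89-0.92 |
| 8-week ramp from half effect | 0.79-0.85 |

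Without period effects the 4- and 8-week ramps from zero give 0.92-0.93 and 0.84-0.86, so most of the loss comes from period adjustment. The immediate-effect row shows that unequal centre exposure does no harm by itself.

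**What a loss would mean.** If the estimate were 80% of the planned effect, chi-square power at a split of about 185 to 215 would be about 56% (delirium) and 60% (cognitive impairment). This is illustrative only, because the planned analysis is a mixed model.

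**The remedy checked.** Giving the first 4 weeks after each switch their own indicator recovers 1.00 of the later effect for a 4-week ramp. With fixed centre effects it raises the 8-week-ramp value from 0.57 to 0.85-0.86. The standard error grows by 7-13%, depending on ICC and period length.

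**The case against.** The strongest reply is that neither premise is written down. The article states no ramp and no 0/1 coding, and exposure coding commonly belongs in an analysis plan, which is not shown here. This stands: the size is conditional and runs from nothing upwards. What remains is that the article describes the design in two phases while wider staff training begins with the second.

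The delivery text can also be read as maintenance. Champions are trained beforehand, the other staff get a short session, and the posters serve to refresh knowledge. This makes a start from zero doubtful, and it is why the half-effect rows are shown.

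The process evaluation will record fidelity, dose and reach. That would help explain a weak result but would not correct the estimate.

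Delirium events in a 4-week window would be few. The window holds 16 of 208 centre-weeks, about 31 of 400 patients, so 31 × 0.009 to 31 × 0.06 gives about 0.3 to 1.9 events. The window's own log-odds may not be estimable. The effect from 4 weeks on is still available if those patients are left out of that one analysis.

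**Conclusion.** The point holds in conditional form. If uptake is gradual and treatment is coded 0/1 with period adjustment, the established effect is understated by about 8-11% (2-week ramp from zero), 15-22% (4 weeks) or 31-43% (8 weeks). The loss is about half that if half the effect is present at the switch, and nil if the effect is immediate. Ramp length, ramp shape, ICC, even accrual, the 52-week reading and the linear scale are assumptions. The planned binary models use a logit link.

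A reader might infer three stronger things, which the document does not support:
- **That the estimate will fall well below the truth.** No ramp is stated, so no loss is established.
- **That the 40-to-16-week spread in exposure itself dilutes the effect.** These are centre-weeks, not patient dose, and with an immediate effect the estimate is unbiased.
- **That a go/no-go decision hangs on this estimate.** No such rule appears. The tests are exploratory, and the Discussion leaves the effect on delirium incidence to later confirmatory studies.

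This is a worthwhile, cheap improvement, not a demonstrated error.

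**What to change.** Keep the as-planned estimate and all recruited patients. Pre-specify beside it one analysis that treats the first 4 weeks after each centre's switch as a roll-out window. Give the window its own indicator, or leave those patients out of this analysis if delirium events are too few for the logit model. Report the effect from 4 weeks after the switch next to the as-planned estimate. State in the plan how exposure is coded.

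The cost is analysis-plan wording and one model term, with no added patients or visits. The standard error of the later effect is about 7-13% larger than that of the one-step effect. The 4-week length is a compromise: for longer ramps part of the bias remains, about 14-15% for an 8-week ramp with fixed centre effects. An 8-week window would raise the standard error by about 31%.
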